##### Responsibilities of each trial groups

Under the guidance of the study director, the trial design group extensively reviews references and information about the subject, designs and adjusts the trial protocol, and collates the clinical data. Detailed information from ward feedback is collected daily, summarized and recorded, and reported to the director twice a week if there are no exceptional circumstances, but cannot be involved in treatment, data collection, or assessment. 

The expert group provides comprehensive guidance on trial design, implementation, and analysis of the results, and the design group reports weekly to it on the progress if no special circumstances occur.

The Ethics Committee and DSMC are responsible for the approval of the trial design and the occasional monitoring of the trial.

Acupuncture and Moxibustion Ward 3 is the main site for the implementation of the trial, from which the patients are sourced and treated, with the medical and nursing staff and the rehabilitation therapists providing accurate operation. They undertake patient treatment, observation, assessment, EEG-sEMG data collection, recording, and dealing with emergencies, which will be summarized by the ward manager and feed back to the design team on a daily basis. If difficulties are encountered, advice is sought from the trial director or even submitted to the expert group for joint discussion.

The third party data processing team processes and analyses the data according to the objective data provided by the design group and is not allowed to ask about anything related to the trial due to blind consideration.

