### Study design

This clinical trial is designed as a double-blind RCT with 90 participants (60 stroke patients and 30 healthy controls) to be recruited. SPIRIT checklist and CONSORT statement were used when writing this study protocol [13, 14]. The whole study duration is about 17 weeks, including the washout period (7 days), the screening observation (3–7 days), the treatment period (3 weeks), and the follow-up period (3 months) (Fig. 1). After signing the informed consent (version date: 2021.11.19, version number: V1.1), all patients will be randomized divided into two groups in a blind manner—programmed flexor–extensor alternating electrical acupoint stimulation group (PES group) and conventional flexor–extensor alternating electrical acupoint stimulation group (CES group) with 30 cases in each, and the treatment will last for 3 weeks (6 days of treatment with 1-day rest per week). Healthy controls are used as a baseline without treatment. Participation in the trial is entirely voluntary, and they can withdraw at any time during the study without any reason. The participants are blinded, and the signal acquisition, evaluation, and outcome assessors are blinded. Because the treatment operation is too programmed, it is difficult to blind the performers. To prevent unblinding, subjects are advised not to discuss treatment options with evaluators (Figs. 2 and 3). All the patients will be followed up for 3 months. The follow-up time points will be at the end of the 1st month and 3rd month after the trial. The data and results will be monitored by the Data and Safety Monitoring Committee (DSMC) and the Ethics Committee.

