### Randomization and blinding

A random grouping method will be adopted. The SPSS 26.0 statistical software is used to randomly generate serial numbers and groups, and blind selection cards are made and put into envelopes (with no difference in appearance). Numbers are according to the inclusion sequence of the subjects, and corresponding experimental groups are entered according to the blind selection cards. Envelope administrators will not participate in this study, and the staff who generate the allocation sequence, enroll participants, and assign participants to interventions will be different ones without communication about the allocation. When patients are treated, the operators should follow the treatment assignment.

The study will be conducted in a double-blind method. Due to the particularity of the operation, the operators (participating doctors and physiotherapists) will not be blinded, but only the electrophysiological indicator collectors, scale evaluators, data recorders, statistical analysts, outcome assessors, and the included subjects are blinded. The operators are not involved in the design of the protocol; thus, they have no determination of the potential differences of each treatment method. They only need to ensure the protocols are followed accurately, so that the treatment and results will not be influenced even though they are unblinded.

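### The responsibilities section gives the ward team that delivers the stimulation the assessment, EEG-sEMG collection and recording tasks that the blinding sections reserve for blinded staff

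*Protocol article*

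**What the plan says.** Three sections of the protocol article deal with who knows the allocation and who does what.

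- **Study design.** Blinding is claimed for participants and for those who acquire and evaluate the data: "The participants are blinded, and the signal acquisition, evaluation, and outcome assessors are blinded". Of the people giving the treatment it says "it is difficult to blind the performers".
- **Randomization and blinding.** The same division is drawn by role: "the operators (participating doctors and physiotherapists) will not be blinded", whereas "only the electrophysiological indicator collectors, scale evaluators, data recorders, statistical analysts, outcome assessors, and the included subjects are blinded". The section adds a reassurance that the operators, having had no part in designing the protocol, will not affect the results despite being unblinded.
- **Responsibilities of each trial groups.** Ward 3 is named as the place where the trial is carried out, "with the medical and nursing staff and the rehabilitation therapists providing accurate operation". The next sentence lists their duties: "They undertake patient treatment, observation, assessment, EEG-sEMG data collection, recording, and dealing with emergencies".

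Two other places bear on the point. The Measurement section says that follow-up staff are blinded. The section on management and safety monitoring lists doctors and physiotherapists separately from data collectors and data registers when it describes training.

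**The concern.** The two stimulation programmes differ in what the operator sets and sees: one is sequenced across joints, the other synchronous. Operators therefore know the arm, as the article accepts. Once they are unblinded, blinded outcome collection is the main protection against observer influence on the comparison of PES with CES.

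That protection matters for these outcomes. The sEMG primary outcome is recorded while the patient is asked to perform a voluntary reaching and retrieving movement, so instruction and encouragement can alter it. MBI, CSS, FMA-U, MMT and Brunnstrom are scored by a rater. If the person instructing or scoring has also run the stimulator, the claim of blinded assessment fails for that measurement. The Study design safeguard, which asks patients not to talk about their treatment with evaluators, then has no effect.

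**Working it through.** No arithmetic applies. The check sets the role statements side by side.

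**Step 1: who is unblinded.** Study design (performers) and Randomization and blinding (participating doctors and physiotherapists) agree that those who deliver treatment know the allocation.

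**Step 2: who delivers treatment.** The responsibilities section names the ward's medical and nursing staff and rehabilitation therapists. This group is wider than the operators of the blinding section, but it includes them.

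**Step 3: compare the six roles declared blinded with the ward team's duties.**

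| Role declared blinded | Given to the ward team? |
|---|---|
| Electrophysiological collectors | Yes, by name (EEG-sEMG collection) |
| Data recorders | Yes, by name (recording) |
| Scale evaluators | Yes, under the general word assessment |
| Outcome assessors | Yes, under the general word assessment |
| Statistical analysts | No; a third-party team |
| Included subjects | Not applicable |

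Four of the six blinded roles overlap with tasks assigned to a team that contains the unblinded operators.

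**Step 4: look for a barrier inside the ward team.** The article writes separations elsewhere. Different people generate the sequence, enrol and assign. The design group is kept out of treatment, data collection and assessment. The third-party analysts may not ask about the trial. No comparable sentence separates treating a patient from assessing that patient.

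**Step 5: which measurements are exposed.** Table 3 and the outcome section give the following:

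- **sEMG (primary):** recorded before and after the first and last treatment. It depends on effort, so it is exposed.
- **Resting EEG with eyes closed (primary):** same times and same conflict of assignment, but no movement and no rating, so there is less room for influence.
- **Five scales at baseline and 3 weeks:** rater-scored, so exposed. At baseline this matters only if allocation is already known. The section on patients and healthy controls puts assessment before random assignment, while Measurement puts randomization before evaluation.
- **Five scales at 1 and 3 months:** Measurement states that the staff are blinded.

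**Step 6: test the reassurance.** Not having designed a protocol does not stop an operator from knowing which programme a patient received. The premise therefore does not support the conclusion, least of all if the same people also collect data.

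**The case against.** The strongest reply is that the responsibilities section is an organisational summary. On that reading the plural pronoun refers to the ward as a team, in which some people treat and others assess. The section that governs blinding separates operators from collectors, evaluators and recorders; the training list does the same; and Study design treats evaluators as people who do not know the treatment. Table 3 also schedules a blinding assessment.

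Much of this stands. The team reading is possible, and the intended design is evidently blinded assessment. But the reply depends on a separation that the article never states for treating versus assessing, although it states others. A blinding assessment can detect a failure but does not prevent one.

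A reader might also infer several stronger things that the document does not support:

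- **That the same individual will treat and assess.** The text shows a conflicting assignment to a group, not to a person.
- **That recordings are made next to the treating staff.** The outcome section gives times only; it gives neither the location nor who instructs the patient.
- **That every outcome is unblinded, so the double-blind label is simply false.** Follow-up ratings are stated to be blinded, resting EEG needs no movement or rating, and the blinding of participants and analysts does not depend on this section.
- **That bias would favour PES.** Both arms receive active stimulation at the same acupoints, and the article does not say that a higher biceps RMS is the better result.
- **That the bias can be sized.** Any percentage would be an assumed observer effect divided by the planned difference of 167.61 − 68.17 = 99.44 RMS units, and would show no more than the assumption put in.

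**Conclusion.** The contradiction is in the current text and should be resolved. The responsibilities section assigns outcome collection, assessment and recording to a group that includes the unblinded operators, while the two blinding statements reserve those tasks for blinded staff. If the section is followed as written, the sEMG primary outcome and the scale ratings at baseline and 3 weeks could be collected by people who know the arm. EEG collection falls under the same conflict but is less open to influence.

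The conclusion rests on the plain meaning of the duties sentence and on the absence of any rule that keeps treating staff from assessing their own patients. It does not establish that unblinded assessment will occur, and no size or direction of bias follows from the document. The point is important because assessor blinding is the trial's main remaining safeguard and because the correction is cheap.

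**What to change.** 1. Reword the responsibilities section to agree with Study design and with Randomization and blinding. State that staff who treat a patient do not instruct, record or score that patient's sEMG, EEG or scales, and that these tasks go to the blinded collectors, evaluators and recorders already named.
2. Remove from Randomization and blinding the assurance that unblinded operators cannot affect results because they did not design the protocol.
3. Trial status gives a recruitment start of 3 June 2022 and an expected duration of 2 months, so data may already exist. Report who collected each outcome. Where treating staff did so, or will do so, drop the assessor-blinding claim for those outcomes.

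The cost is revised wording and rostering. The blinding section already presumes separate blinded collectors and evaluators, so no role is needed beyond those planned. The downside is less flexibility in who covers an assessment on the ward.

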## Discussion

In the process of motor function recovery in stroke patients, flexor and extensor coordination disorder is a common symptom [26, 27]. At present, the theoretical basis of limb function rehabilitation of apoplexy mainly includes brain plasticity theory and limb movement control theory [28]. Patients show the spasticity pattern of the upper limb flexor and lower limb extensor [29]. Therefore, stimulation of the flexor or extensor muscle alone is not enough. Abnormal movement patterns can affect the recovery of motor function and cause wrong posture, which needs to be corrected timely.

Rehabilitation of the upper limbs is difficult and time-consuming. This instrument is combined with the advantages of FES and acupoints. By stimulating the corresponding acupoints of the active and passive muscle groups of the upper extremity at low frequency, the contractile ability of the muscles is enhanced, and the relaxation and contraction function of the active and antagonistic muscle groups is coordinated, to effectively improve the motor function of the affected limb and promote the recovery of the central nervous system.

Six months is a gold period for rehabilitation after stroke [30]. But due to the COVID-19 epidemic, treatment has affected many patients. Rehabilitation training should be initiated soon after the stroke condition stabilized for better recovery effect [31]. The instrument is portable, easy to use, non-invasive and painless, and low cost, which may be easy to be accepted at home or in the community.

This study is a double-blind RCT. The safety and efficacy of the instrument are beyond doubt after 20 years of clinical application and many clinical studies [32–34]. This study improved the previous electrical stimulation output strategy, formed into a programmed one. Through the evaluation of neuro-electrophysiology and scales, the curative effects will be visualized and objectified for better interpreting the difference in the two stimulation methods, which may provide a new reference for integrated traditional Chinese and Western medicine in the treatment of motor function recovery after stroke.

## Trial status

The recruitment began on 3 June 2022 and is expected to last for 2 months (version date: 2021.11.19, version number: V1.1).

## Data Availability

Trial data are available on reasonable non-commercial request to the investigator of the study.

## Abbreviations

RCT: Randomized controlled trial
FES: Functional electrical stimulation
TCM: Traditional Chinese medicine
PES: Programmed flexor–extensor alternating electrical acupoint stimulation
CES: Conventional flexor–extensor alternating electrical acupoint stimulation
EEG: Electroencephalography
sEMG: Surface Electromyography
MBI: Modified Barthel Index
CSS: China Stroke Scale
FMA-U: Fugl-Meyer Assessment Upper Limb
MMT: Manual Muscle Testing
GBD: Global Burden of Disease
ADL: Activities of Daily Living
SPIRIT: Standard Protocol Items: Recommendations for Interventional Trials
CONSORT: Consolidated Standards of Reporting Trials
DMSMC: Data and Safety Monitoring Committee
RMS: Root mean square
MF: Median frequency
BB: Biceps brachii
TB: Triceps brachii
ECR: Extensor carpi radialis
B: Brachioradialis
ED: Extensor digitorum
FCU: Flexor carpi ulnaris
iEMG: Integrated Electromyography
MPF: Mean power frequency
SOP: Standard operation procedure
CRF: Case Report Form
EDC: Electronic Data Capture
ANOVA: Analysis of variance
